## Abstract

**Background:**

To improve communication of risk messages, they must be communicated in a way that is understandable and relevant to the patient. Communicating risk of cardiovascular disease is a complex and individualised task, since the risk itself is a combination of multiple personal risk factors. Raised blood pressure is but one of these risk factors. In Denmark, only one-third of hypertensive patients are adequately treated, with regards to national clinical guidelines. One reason for this problem is low treatment adherence; tools with documented effects for increasing adherence of patients are limited.

Our objective is to evaluate the effect of a personalised, interactive and dynamic risk-assessment and risk-communication tool: ‘Your Heart Forecast’ (YHF) on blood pressure control, primary non-compliance, health literacy and patient empowerment.

**Methods:**

Cluster-randomised controlled trial in general practice. Effect measures are adherence, blood pressure, lipid levels and empowerment at inclusion and after 6 and 12 months. To identify other benefits or possible adverse effects of the intervention, qualitative interviews will be conducted with a subgroup of patients.

**Discussion:**

The investigators will explore effects of Your Heart Forecast on patients’ health literacy, adherence, empowerment and blood pressure control. The DANish evaluation of Your heart forecast (DANY) project will be the first to rigorously evaluate effects of YHF in Denmark and to link adherence of hypertensive patients exposed to YHF with the national databases of prescriptions and health services provided.

**Trial registration:**

Clinicaltrials.gov, NCT04058847. Registered on 16 August 2019.

## Background

To improve communication of risk messages, they must be communicated in a way that is understandable and perceived relevant to the patients’ personal life and health. Every individual has their own beliefs, values and understanding, as well as social and psychological background. Therefore, communication tools must be personalised and easy to understand. It is important to bear in mind when designing communication tools, that close to half of the European population has a low degree of health literacy [1], which is associated with poor health outcomes, low self-management and underestimation of personal risk of cardiovascular disease (CVD) [2]*.* Since the risk of CVD is the product of a complex combination of multiple individual risk factors, there is a need for communicating complex information in an easy understandable way. Several tools for calculating and communicating risk of CVD have been developed, but rigorous testing of their communicative effects is sparse.

Adherence is generally low for preventive interventions addressing risk of CVD [3]. Most patients do not feel unwell despite their diagnosis of hypertension or hypercholesterolaemia, and combined with an underestimation of their personal risk, this might be the reason for low adherence to preventive treatment.

In Denmark, general practitioners (GPs) are encouraged by clinical guidelines to conduct an annual blood pressure control assessment for patients with hypertension in order to reach guideline-described levels of blood pressure and to reduce other known risk factors of CVD as well [4–6]. The annual blood pressure control assessment represents a unique and regular opportunity for the GPs to motivate their patients to achieve healthier lifestyles and better adherence to treatment. However, despite all good intentions, 7/10 Danish patients diagnosed with hypertension have inadequately controlled blood pressure [7, 8].

Inadequately controlled blood pressure is associated with an increased risk of CVD and more frequent contact with GPs. Intention to change behaviour is related to the patients’ perception of risk [9]. Consequently, better ways for GPs to communicate risks of CVD and motivate patients for risk-reducing strategies are warranted. Efficient communication requires information to be presented in formats that encourage decision makers, i.e. patients, to automatically extract specific meanings or overall messages [10]. Use of graphical illustrations with distinct features has previously been shown to be an effective and user-friendly tool to communicate risk, especially to people with limited health literacy [2, 10, 11]. A visual decision aid could be a way to improve the blood pressure consultations and to assure that GPs are supported to provide patients with the relevant information. It is suggested that using a decision aid will also systematise the consultation and make it more reproducible [12].

The present study will use the Internet-based risk communication tool Your Heart Forecast (YHF) to evaluate whether it can influence patients’ understanding of risk and adherence to treatment. This will be done paying special attention to patients’ blood pressure, lipid levels, empowerment and health literacy. The rationale behind the tool is to help improve patient–doctor interaction and communication so that the patient can gain an improved understanding of his/her risk of CVD and the modifiability of risk. Patients with hypertension have been chosen as a case study, since high blood pressure is one of the main modifiable risk factors for CVD, as opposed to, for example, age, gender, ethnicity and family history.

YHF is a risk-communication tool, which communicates risks of CVD as personalised, interactive and dynamic visual graphs. Following input from personal health-related data, the GP can, by using YHF, interactively guide the patient through:
their currently predicted five-year absolute risk of CVD;the age at which they would achieve their currently predicted risk of CVD if they had ideal/achievable risk factor control (the heart age);their predicted risk of CVD as they get older (the heart forecast);their future risk of CVD if their current risk factors are improved.

To succeed in behavioural changes, the patient can be helped in several ways in a setting such as general practice. From the perspectives of the Transtheoretical theory/Stages of Change theory [13] and the Information-Motivation-Behavioural Skills theory [13], the present intervention helps patients in several ways as follows. YHF gives the information of risk of CVD in a new way and at the same time offers a motivation as it immediately and visually shows the number of years you can add before reaching a condition where pharmaceutical treatment is highly recommended. As such, YHF presents the information leg as well as the motivation leg from the Motivation-Behavioural Skills theory, which together is expected to strengthen the patient’s behavioural skills and to add to the likelihood of sustaining a behavioural change.

As it has previously been demonstrated that single event interventions do not have an effect if not followed up, YHF will be introduced in a package deal. YHF will function as the primary intervention and repeated reminders via e-mail will be the secondary component. Patients in the intervention group will, after the consultation with the GP, receive emails every other week, as part of a general health literacy educational program.

The second part of our planned intervention, the reminding e-mail program, aims at the action and maintenance stages regarding the Transtheoretical theory [14]. Every other week, patients in the intervention group will receive an email with a piece of advice on how to live healthier. In the same email, a reminder and a link are inserted, through which the patient can play back the information given at the blood pressure consultation at the GP using YHF. The email program offers the possibility of boosting the patients’ motivation and by that support the ongoing behavioural change.

## Methods/Design

### Aim

The aim is to evaluate the effect of using the YHF visual communication tool on changes in blood pressure and adherence to CVD preventive medications. Further, by means of questionnaires, the aim is to study whether changes in health literacy, adherence, patient empowerment and risk communication are associated with changes in blood pressure, lipid levels and/or lifestyle choices. By means of qualitative interviews, it will be investigated whether the use of the program heightens motivation, increases awareness of risk or creates unwarranted effects such as causing the patients to be anxious.

### Research question

#### Primary research question

Will the introduction of YHF during an annual blood pressure control consultation lead to improved general health literacy, improved adherence to medication and empowerment after 12 months?

#### Secondary research questions

Will blood pressure be reduced among patients in the intervention group compared to the control group after 12 months?Will lower health literacy and/or low empowerment at baseline be associated with higher blood pressure at baseline?Will health literacy and/or empowerment be improved after 6 and/or 12 months among patients enrolled in the intervention group?Will increased health literacy and/or empowerment be associated with healthier lifestyle including diet, exercise and smoking habits after 12 months?Will there be subjective feelings of increased motivation or sickening after introducing the intervention?Will risk of CVD be lower among patients in the intervention group compared to the control group after 12 months?

### Clinical relevance

Low medication adherence is a significant health, time and cost-consuming challenge for patients with increased blood pressure as well as for their GPs.The study is not only relevant for the individual patient, but due to the very high prevalence of increased blood pressure, also of significant societal relevance.The study will address this clinically relevant challenge through improved risk communication and efforts to improve health literacy.Increased health literacy will most likely lead to fewer visits to the GP, better adherence, lower degree of complications and, thus, higher quality of life for the patient and fewer health costs for society.

### Trial design

This study will use a mixed methods approach with a combination of a randomised controlled trial (RCT) and qualitative semi-structured interviews. The protocol has been developed using the SPIRIT checklist as guideline (see Additional file 1).

Participating general practices will be cluster randomised into two groups, an intervention and a control group. The randomisation will be done using REDCap’s randomisation tool. Two general practices will function as pilot practices and be enrolled as if they were intervention practices. In these two practices, patients will be assessed 3–6 months before the project practices. A subgroup Q, of 5–15 patients from the pilot group, will be selected for qualitative interviews.

GPs in the control group will not be introduced to YHF and will follow their patients in the blood pressure control program as usual.

### Study population

#### Participants

All general practices in the Region of Southern Denmark will receive a postally distributed, written invitation to an information meeting about the RCT. Practices not attending the meetings will, in following inclusion rounds, be offered an introduction to the trial via video meetings. Of those GPs willing to participate, 30 will, with due respect for geographical location and practice type, be representatively selected for participation.

Both incident and prevalent hypertensive patients will be included within an inclusion period of 6–12 months.

### Sample size

Calculation of sample size is based on blood pressure as primary outcome. For a two-sample pooled *t* test of a normal mean difference with a two-sided significance level of 0.05, a sample size of 120 participants per group is required. This is to obtain a power of at least 90%, to detect a difference of 5 mmHg between the means at baseline and after one year. To adjust for expected drop-outs, 30 participants will be added per group and at least 300 patients will be enrolled in the trial. To account for cluster-effects when randomising on practice level, the sample size will be further increased by 10%–15% to reach 340 patients. More participants will be needed for subgroup analyses on sociodemographic and, therefore, the aim is to reach a total of 600 participating patients. The pilot practices will provide information regarding the prevalence of patients with inadequately controlled blood pressure willing to participate, as well as more specific knowledge on the needed number of practices included, making the final sample size calculation uncertain at this point.

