**Fig. 2 Fig2:**
[figure not shown]
SPIRIT figure

The questionnaire (q_1_) will include questions to evaluate socioeconomic and sociodemographic variables, baseline health literacy, risk perception and self-efficacy (PAM-13 [15]), smoking status, co-morbidity and medication.

The second patient questionnaire (q_2_) is very short and will be sent out by email approximately two weeks after the first questionnaire and the informed consent has reached the research group. This questionnaire will focus on whether the patient was surprised about the risk score, if any changes in the medication were made and how the general experience of the YHF is. In this email, the intervention group will be informed that they have been selected to receive an email every second week with information about general health literacy, risks of CVD and advice regarding risk reduction.

Six months after enrolment (t_6_) participants will be asked to answer the first questionnaire (q1) again.

Data regarding blood pressure will be obtained through questionnaires at baseline and after the first annual blood pressure control (t_12_), where blood pressure should also be measured as an ambulatory blood pressure. Data regarding number and content of contacts to the GP will be obtained from the patient’s medical records and the affiliated accounting system including prescription databases for estimating compliance. All telephone consultations, email consultations, clinic consultations and home visits are registered. Contacts will be obtained from three years before and up until two years after the intervention.

Patients in the intervention group will receive their personal profile in the YHF to make it possible for them to access and use the program at home in between the blood pressure consultations at their GP. To gain access to their profile from home, they shall use a personal link sent by email at the end of the blood pressure consultation with their GP. All data entered in YHF will be stored in accordance with Danish law by the software provider, with whom a data management agreement has been made.

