### Clinical implications/perspectives

It is expected that using YHF will improve health literacy and patient empowerment, increase adherence to medication and lower patients’ blood pressure. Further, socio-demography is expected to have a significant impact on these outcomes. If the introduction of YHF is shown to significantly improve patient adherence or reduce hypertension, it should be implemented on a larger scale. By using YHF, focus is moved towards patients’ total risk of CVD instead of just hypertension.

The wider perspective of the present trial is the generic potential that improved risk communication through a dynamic and interactive communication tool can change not only empowerment, understanding and relevant health outcomes for CVD, but also for other diseases.

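### The sample size treats blood pressure as the primary outcome, but the research questions make it secondary and give three other outcomes as primary, for which no sample size basis is stated

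*Protocol article*

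**What the plan says.** The protocol article ranks its outcomes in several places, and the rankings differ.

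- **Sample size:** "Calculation of sample size is based on blood pressure as primary outcome". The section gives 120 per group, a difference of 5 mmHg, two-sided 0.05 and at least 90% power. It does not say whether systolic or diastolic pressure is meant.
- **Primary research question:** whether introducing the tool will "lead to improved general health literacy, improved adherence to medication and empowerment after 12 months". Blood pressure is not mentioned.
- **Secondary research questions**, first item: "Will blood pressure be reduced among patients in the intervention group compared to the control group after 12 months". A later item asks about health literacy and/or empowerment at 6 and/or 12 months in the intervention group, so these two appear at both levels.
- **Aim:** leads with "changes in blood pressure and adherence to CVD preventive medications".
- **Abstract, objective:** effect "on blood pressure control, primary non-compliance, health literacy and patient empowerment", unranked.
- **Abstract, methods:** "Effect measures are adherence, blood pressure, lipid levels and empowerment at inclusion and after 6 and 12 months". This list is also unranked, and it omits health literacy.
- **Outcome measures and statistical analysis:** gives methods for blood pressure, number of GP visits and the PAM13 score, and calls none of them primary.
- **Clinical implications/perspectives** (Discussion): "If the introduction of YHF is shown to significantly improve patient adherence or reduce hypertension, it should be implemented on a larger scale".

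**The concern.** A trial's stated power and its main claim should refer to the same outcome. Here the outcome used for sizing is excluded from the primary question, and the outcomes in the primary question are not used for sizing.

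Two things are at stake. First, a null result on health literacy, adherence or empowerment could not be interpreted from the stated 90%, because that figure was derived for a blood pressure difference. Second, the article gives textual support for calling either blood pressure or the other three outcomes primary. The choice should be fixed before results are known. This matters the more because the analysis section says that the authors have access to all data as they are generated, even though a blinded statistician will run the analyses.

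**Working it through.** **1. What the stated sample size covers.** Inputs from the Sample size section: n = 120 per group, difference 5 mmHg, two-sided alpha 0.05, power 90%. No standard deviation (SD) is stated, so 120 cannot be reproduced directly. Solving the two-sample formula for the SD:

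SD = 5 × √(120/2) / (1.960 + 1.282) = 38.73 / 3.242 ≈ 11.95 mmHg

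The exact t-test version gives 11.90. With an assumed SD of 12, n is 122 (normal) or 123 (t), close to 120. For a range of assumed SDs, the normal formula gives 85 per group at SD 10, 190 at SD 15 and 337 at SD 20. The figure of 120 is thus coherent as a blood pressure calculation with an SD near 12 mmHg.

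The later steps only scale this number:

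- Drop-out: 120 + 30 = 150 per group, 300 in total.
- Clustering: 300 × 1.10 = 330 and 300 × 1.15 = 345, which brackets the stated 340.
- The increase to 600 is justified by subgroup analyses.

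No step uses an effect size or variability for health literacy, adherence or empowerment.

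**2. The ranking, section by section.**

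| Section | Blood pressure | Health literacy | Adherence | Empowerment |
|---|---|---|---|---|
| Sample size | primary | – | – | – |
| Primary research question | – | primary | primary | primary |
| Secondary research questions | secondary | secondary | – | secondary |
| Aim (lead sentence) | lead | – | lead | – |
| Abstract, objective | unranked | unranked | unranked (as primary non-compliance) | unranked |
| Abstract, methods | unranked | not listed | unranked | unranked |
| Statistical analysis | unranked | not named | not named | unranked (PAM13) |

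The first three rows contradict each other, and none of the others resolves them.

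**3. Illustration of what an open choice could mean.** Suppose k outcomes were each tested at two-sided 0.05, any one sufficed, and the tests were independent. Under the null, the chance of at least one significant result is 1 − 0.95^k, and in the beneficial direction only it is 1 − 0.975^k.

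| k | Either direction | Beneficial direction only |
|---|---|---|
| 2 | 9.75% | 4.9% |
| 3 | 14.3% | 7.3% |
| 4 | 18.5% | 9.6% |

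With an assumed correlation of 0.5, simulation gives about 9.1%, 12.5% and 15.6% for either direction. The protocol states no such any-one-suffices rule for its primary outcomes, so these are not its error rates.

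**4. Timing.** The abstract lists blood pressure and lipids at 6 months. The Practical procedure and Data collection sections place blood pressure follow-up at the annual control (t12) and describe no 6-month visit. For the questionnaire, Data collection says that at six months "participants will be asked to answer the first questionnaire (q1) again". It does not say whether q1 is repeated at t12.

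**The case against.** Four objections deserve an answer.

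- **The implementation sentence is not a success rule.** A reader might infer that the trial succeeds if either adherence or hypertension improves. The sentence is a remark about roll-out in the Discussion and defines neither an endpoint nor a decision rule. This objection stands.
- **Multiplicity may be handled elsewhere.** A reader might infer that the error rate is uncontrolled. An analysis plan may exist that is not shown, so the absence of a procedure here is no finding. The primary question also joins its outcomes with *and*. Read literally, all must improve, and that requirement would not inflate the error. This stands too, which is why the percentages above are illustrations only.
- **The 12-month questionnaire may well be planned.** A reader might infer that health literacy and empowerment are measured at 6 months only. The text does not say so: the abstract lists empowerment at 12 months, blood pressure is collected by questionnaire after the t12 control, and the SPIRIT figure is not shown. What remains is a request for confirmation.
- **The registration may name the primary outcome.** It is cited but cannot be seen here. Even if it does, the article's own sections still disagree.

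None of these touches the conflict between the Sample size section and the research questions. It lies in what the article states, so neither condensation nor an unseen plan explains it: a plan consistent with one section would contradict the other.

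**Conclusion.** The point holds as an internal contradiction about which outcome is primary. The stated 90% power (120 per group, 5 mmHg) belongs to an outcome that the objectives call secondary, and none of the three outcomes in the primary question has a stated sample size basis. This rests on the text alone and needs no assumption about the SD, the correlation between outcomes or the content of an analysis plan.

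Its size is best expressed as three primary-question outcomes without a power statement, and one power statement attached to a different outcome. It does not show that the trial has an either/or success rule, an inflated type I error or no 12-month measurement of the questionnaire outcomes. The abstract's 6-month blood pressure and lipid measurements are a minor wording point with no bearing on which outcome is primary.

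**What to change.** Before outcome data are analysed, choose one of two routes.

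1. **One primary outcome (the natural choice).** Name the between-arm difference in 12-month blood pressure, with systolic or diastolic specified. The trial was sized on blood pressure, so the stated power then belongs to the primary outcome. Health literacy, adherence and empowerment become secondary.
2. **Keep the three outcomes of the primary question.** State how they combine, give a power statement for each, and say that the 90% applies to a secondary outcome.

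Then align the abstract, Aim, Primary and Secondary research questions, Sample size, and Outcome measures and statistical analysis sections. Word the implementation sentence in the Discussion so that it rests on the primary outcome.

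Minor: reconcile the abstract's 6-month blood pressure and lipid measurements with the Practical procedure and Data collection sections, and confirm that q1 is also administered at t12.

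The first route costs wording only, plus q1 at an existing t12 questionnaire contact if it is not already scheduled there. The second also needs assumptions and a calculation for each of the three outcomes.
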